#### Eating style

To assess eating styles, the German version of the Dutch Eating Behavior Questionnaire - DEBQ [49–51] will be used. The DEBQ is a questionnaire consisting of 30 items with three different subscales for the eating styles: *Emotional eating* (eating due to an emotional state, such as anger or sadness), *restrained eating* (restricting food intake due to weight concerns), and *external eating* (eating because of external cues, such as the sight or smell of delicious food). For various statements, such as for emotional eating “When I feel lonely, I would love to eat something”, the degree of agreement is recorded from 1 (‘never’) to 5 (‘very often’). Total scores for the three subscales will be calculated. Higher values indicate a stronger expression of the corresponding eating style. Overall, the German version of the DEBQ shows good psychometric properties [51].

#### Dietary behavior

For the purpose of the intervention, the dietary intake questions are closely linked to sub-behaviors targeted in the intervention. Therefore, a list of 12 food groups has been formulated. Participants will be asked to indicate the average intake frequency for a usual week ranging from 0 (‘never’) to 5 (‘every day’). Hereafter, the average portion per day has to be chosen from a list of predefined portions (in grams accompanied by real life examples) specific for each food group. The list consists of the following food groups: a) vegetables, b) fish, c) meat, d) meat replacement products/eggs, e) fruit, f) processed pasta/rice, g) potatoes/whole grain pasta/whole grain rice, h) sweet and savory snacks, i) seeds and nuts j) whole grain bread, k) white bread, l) sugared drinks (fruit juice/sugar sweetened soft drinks).

#### Physical activity

Physical activity behavior will be assessed using the German short version of the International Physical Activity Questionnaire [52]. This questionnaire was developed to gather data about weekly physical activity of adults between the ages of 15 and 69 and shows acceptable psychometric properties [53]. In seven items, participants are asked to self-assess how many days out of the last seven days they did vigorous, moderate or walking activities and on those days how many hours and minutes they spent on each particular physical activity level. Time spent sedentary on a weekday is assessed as hours per day.

#### Depressive symptoms

Parental depressive symptoms will be assessed using the German version of the Edinburgh-Postnatal-Depression-Scale [54]. The EPDS is a 10-item self-report questionnaire for the screening of postpartum depressive symptoms in mothers and fathers [55, 56]. Items are rated on a 4-point-Likert scale ranging from 0 to 3. The overall score ranges from 0 (‘no postpartum depression’) to 30 (‘severe postpartum deprerssion’). Cox et al. (1987) report satisfactory psychometric properties.

#### Emotion regulation

Emotion regulation will be assessed through the short form of the Difficulties in Emotion Regulation Scale (DERS-18) [57, 58]. The questionnaire contains six subscales (*nonacceptance of emotional responses, difficulty engaging in Goal-directed behavior, impulse control difficulties, lack of emotional awareness, limited access to emotion regulation strategies and lack of emotional clarity*) with two to four items each (18 in total) that are rated on a 5 point-Likert scale ranging from 1 (‘almost never’) to 5 (‘almost always’). Overall, the DERS-SF showed good psychometric properties [59].

#### Experiences in close relationships

To assess partnership quality, the German version of the Experiences in Close Relationships-Revised (ECR-R) questionnaire will be used [60]. It is a 9-item short version to assess attachment anxiety and avoidance in adult partnerships. Participants rate statements concerning their partnership on a 7-point Likert scale ranging from 1 (‘strongly disagree’) to 7 (‘strongly agree’). Overall, the ECR-R has good psychometric properties [60].

#### Self-Efficacy

General self-efficacy will be assessed by the German version of the General Self-Efficacy Scale (GSE) [61]. The GSE assesses general optimistic self-beliefs to cope with difficult situations. It consists of 10 items, asking for one’s competence to cope with a range of challenging situations (e.g., ‘I can always manage to solve difficult problems if I try hard enough’). Responses to each item are given on a 4-point scale ranging from 1 (‘not at all true’) to 4 (‘exactly true’). To obtain a score for perceived self-efficacy the answers to the single items are summed up into one score. The GSE shows acceptable psychometric properties [62].

#### Parental childhood maltreatment

The Childhood Trauma Screener (CTS) is the German short form of the Childhood Trauma Questionnaire (CTQ) with five items [63, 64]. The CTS will be used to assess parental childhood maltreatment experiences. Participants rate emotional, physical, and sexual abuse as well as emotional and physical neglect on a 5-point-Likert scale ranging from 1 (‘not at all’) to 5 (‘very frequently’). Based on a validation study, high adversity was defined by scores higher than 10 [65].

#### Parenting stress

The German Version of the Parenting Stress Index – Short Form [66, 67] will assess the parental stress during the postpartum period. The self-report questionnaire contains 28 items with seven subscales. Each subscale includes four items rated on a 5-point Likert-scale ranging from 1 (‘strongly disagree’) to 5 (‘strongly agree’) with higher scores indicating higher levels of stress. Studies showed that the psychometric properties are good [66–69].

#### Parent-Child interaction

Parent-child interaction will be assessed by the German version of the Postpartum Bonding Questionnaire [70]. Originally, the questionnaire was developed as a screening instrument in order to diagnose bonding disorders consisting of 25 items yielding scores on four factors [71]. The German version consists of 16 items. The response categories range from 0 (‘always’) to 5 (‘never’) on a 6-point Likert scale with a higher sum score indicating impaired bonding. The sum scores range between 0 and 80 points. Reck et al. [70] report satisfying psychometric properties.

#### Parental perception of infants’ emotions

The IFEEL pictures (Infant Facial Expressions of Emotion from Looking at Pictures) ([72] have been employed previously in parents at risk for obesity and psychosocial stress to measure their ability to recognize children’s emotions [73, 74]. Six positive, six negative and four ambiguous pictures will be included in the current study, identified by Liel et al. [74] . Pictures are categorized as positive (negative) if rated as positive (negative) by at least 70% of the participants [75]. The internal consistency of positive/negative IFEEL Pictures was excellent for mothers and fathers [74].

#### Regulatory disorders

To gauge the potential stress by a present regulatory disorder, families will be asked to rate how burdened they are by the crying, sleeping and eating behavior of their child. For each of these three areas, families will answer one question, each on a 4-point Likert scale and ranging from 0 (‘not at all’) to 4 (‘very’). For eating behavior – since this is a special focus of this study, two additional questions will be asked that measure diagnostic criteria of an undereating disorder [76].

#### App usability

In order to assess app usability the German version of the mHealth app usability questionnaire for standalone mHealth apps (MAUQ; patient version) will be used [46, 77]. The questionnaire consists of 18 items, which are rated on a scale from 1 (‘strongly disagree’) to 7 (‘strongly agree’). Psychometric properties were rated as very good [46, 77]. The MAUQ has a three-factor design comprising the subscales ‘ease of use’ (5 items), ‘interface and satisfaction’ (7 items), and ‘usefulness’ (6 items).

#### App usage

The quantitative (i.e., login, logout times, sessions and modules completed, time spent in the app) and qualitative (i.e., participants input, used features, content utilized) app usage and engagement will be assessed by the apps’ meta-data log files. The fundamental data are internally tracked within the app and downloaded to secure servers. Treatment adherence will be operationalized as time spent using the app, numbers of days using the app and worked-through sessions and modules. If variance of data allows for it, we will define user patterns (e.g., heavy vs. minimal users) as outcome and mediator variables.

### Data collection and management

Data will be collected through three (Germany) or four (Austria) online assessments. Participating mothers and fathers complete the questionnaires separately, so that we will receive at least one questionnaire per family (from the mother) for every time point. Links to the assessments are sent out to the families at the corresponding time points (see the description of the procedure above for more details). The questionnaires should ideally be completed in the days after the family receives the link and not later than one month after that. If this period is exceeded at t1, participants will be excluded from this measurement point, but will still receive invitations to later time points. Furthermore, there will be two short online surveys for the HPs gathering information about their professional background and the families’ exclusion and inclusion criteria. We will also collect app-usage data from participants of the intervention arm. The data will be kept in accordance with the data protection guidelines of the European Union. Contact details will be maintained separately from questionnaire data. The collected data will only be marked with the individual study codes. The list with codes will be kept separately and is password protected.

### Blinding

For reasons inherent to the type of the interventions, participants cannot be blinded for the intervention. Families will be told about the group assignment of the HPs during the recruitment process. Statistical analyses will be performed blinded for allocation.

### Statistical analyses

In multilevel analyses, we will assess whether the clustered nature of the data (individuals clustered within families and HPs) has an effect on the results. If present, the impact of the intervention on the primary outcome and secondary outcomes will be analyzed using multi-level-models. If not, linear regression analysis will be used. Analyses of intervention effects will be based on the intention-to-treat principle. Given the cluster randomized design of the study, analyses on intervention effects will be adjusted for baseline values of the outcome. If suitable, missing data will be checked for randomness and be imputed using multiple imputations. Furthermore, we plan to assess the influence of moderating (stressful life events, parent child interaction, social support, partnership quality) and mediating (emotion regulation, self-efficacy) variables to identify determinants and pathways for the intervention’s efficacy and unhealthy weight gain during pregnancy and postpartum.

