### Sample size calculation

For the primary outcome (weight), we have calculated in G*Power that we need to recruit 100 families in each study arm, based on two-sided testing with alpha of 5%, and assuming 20% drop out in order to have at least 80% power to detect a 2 kg difference in weight gain/retention between intervention arms. This is based on the intervention effect on gestational weight gain of the DALI intervention (Simmons D: JCEM 2016), and assuming non-significant clustering in weight within HPs. With this sample size, a 0.45 (SD 1.0) difference in birthweight z-score or infant BMI z-score can be found with 80% power. Since both trials will initially be analyzed separately and assuming non-significant clustering in weight within HPs, clustering by country (Germany, Austria) is not considered in the sample size calculation. Based on previous exchange with HPs, we estimated 2-4 families per HP as realistic. Therefore we intend to recruit at least 60 HPs in each study arm.

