### Randomization

Cluster randomization was chosen to prevent contamination of the different conditions. This means that every HP should provide the same treatment to all of their families participating in the I-PREGNO study. Participating HPs will be randomly assigned to one of the two study arms and will be informed about the assignment immediately. The randomization will be performed using a computerized random number generator, pre-stratified for the two trials provided by an external, independent expert from the Department of Computing in the Cultural Sciences at the University of Bamberg.

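### The article lets a preliminary check with no stated criterion decide whether a trial randomised by healthcare professional (HP) is analysed with or without allowance for clustering

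*Protocol article*

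**What the plan says.** The Randomization section makes the HP the unit of allocation: "Participating HPs will be randomly assigned to one of the two study arms". The reason given is contamination, so "every HP should provide the same treatment to all of their families participating in the I-PREGNO study".

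The Statistical analyses section sets a two-step rule. Step one: "we will assess whether the clustered nature of the data (individuals clustered within families and HPs) has an effect on the results". Step two: if clustering is present, the primary and secondary outcomes "will be analyzed using multi-level-models. If not, linear regression analysis will be used". The article does not say what counts as an effect on the results. The only adjustment it ties to the design is this: "Given the cluster randomized design of the study, analyses on intervention effects will be adjusted for baseline values of the outcome".

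The Sample size calculation section states "we need to recruit 100 families in each study arm", with 20% dropout and clustering within HPs assumed to be non-significant. On cluster size, "we estimated 2-4 families per HP as realistic". It aims for at least 60 HPs per arm.

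**The concern.** Families of one HP are allocated together, so the standard error of the arm comparison has to reflect any correlation between them. HP effects are plausible: HPs deliver the counselling and choose its messages with each family. In Germany they also screen and register families after learning their own allocation.

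Under the written rule, the randomised unit can leave the model because a check was negative. With a few families per HP, a negative check is weak evidence that the correlation is zero. If it is not zero, plain regression gives standard errors that are too small. Adjusting for baseline does not cure this, because it does not model the correlation that remains within HPs.

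The missing criterion is a second weakness. One reading is that results with and without clustering are compared, so the model would be chosen after both answers are known. Masking the arm labels does not hide a p-value.

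At stake are the intervals and p-values of the primary and secondary outcomes in both trials.

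**Working it through.** **Inputs from the article.** 100 families per arm, 20% dropout (80 analysed), two-sided 5% alpha, 80% power, z-score difference 0.45 with SD 1.0, 2-4 families per HP, at least 60 HPs per arm. The article gives no ICC.

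**Assumptions.** ICC 0.05 to 0.10, a 5% F-test as the check, equal cluster sizes, no baseline adjustment.

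**1. The plan's own figure.** n per arm = 2(1.960 + 0.842)² / 0.45² = 77.5, so 78, and 78/0.8 gives 98. The exact t-test gives 79, and 79/0.8 gives 99. The stated 100 is reproduced, as an individually randomised comparison with design effect 1. The 2 kg target cannot be checked directly because no SD is stated.

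**2. Plain regression when HP clustering exists.** Design effect DE = 1 + (m − 1) × ICC. True alpha = 2[1 − Φ(1.96/√DE)].
- m = 2, ICC 0.05: DE = 1.05, alpha 5.6%.
- m = 3, ICC 0.05: DE = 1.10, alpha 6.2%.
- m = 4, ICC 0.10: DE = 1.30, alpha 8.6%.

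**3. The two-step rule.** Simulated null trials: F-test for HP at 5%, then a cluster-level t-test if significant and an ordinary t-test if not (20,000 runs per setting).

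| HPs per arm × families | ICC | Check detects it | Error, two-step rule | Error in trials where the check misses it |
|---|---|---|---|---|
| 40 × 2 | 0.05 | 11.4% | 5.3% | 5.7% |
| 27 × 3 | 0.05 | 15.4% | 5.4% | 6.0% |
| 20 × 4 | 0.05 | 19.0% | 5.9% | 6.9% |
| 40 × 2 | 0.10 | 22.0% | 5.5% | 6.1% |
| 27 × 3 | 0.10 | 33.9% | 5.9% | 7.3% |
| 20 × 4 | 0.10 | 42.1% | 6.3% | 8.7% |

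Always allowing for HP gave 4.7-5.1% in these settings. Repeat simulations put the two-step error at about 5.3-6.5% and detection at up to 43%. With a true ICC of zero the two-step rule gave 4.5-4.9%, so nothing is lost.

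**4. More HPs, fewer families each.** If 60 HPs per arm applies to each trial, 80 analysed families is 80/60 = 1.3 per HP. The two-step error is then about 5.1% at ICC 0.05 and 5.3-5.5% at 0.10. If 60 covers both trials, so about 30 per arm in each, it is about 5.6-5.7% and 5.9-6.1%.

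**5. The family level.** This arises only if parents share a model. Suppose half of families include a father. Mean members modelled = 1.5, mean square = 0.5 × 1 + 0.5 × 4 = 2.5, and DE = 1 + (2.5/1.5 − 1)ρ. For ρ = 0.1 to 0.3, DE = 1.07 to 1.20. Dropping the family level then gives alpha of 5.8-7.4% from that level alone. The share of fathers and ρ are assumptions.

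**The case against.** The strongest reply is that the effect is small and rests on supplied assumptions. Much of that stands.

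- **The ICCs and the 5% test are not in the article.** With a 20% threshold, the two-step error in the 2-4 families settings is about 4.9-5.4%, which is close to nominal. This is an average, however. Trials that still pass to plain regression under that threshold run at about 5.7-9.1%.
- **The 20 × 4 setting gives the top figures and is the least likely.** It has fewer HPs than either reading of the recruitment target, and dropout would thin 2-4 recruited families to about 1.6-3.2 analysed.
- **Baseline adjustment may absorb case-mix differences between HPs** and lower the residual ICC. It does not replace a cluster term, but the figures above are for unadjusted outcomes.
- **A comparison of results with and without clustering might switch models when it matters.** That is possible, but the article does not say so.

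Three stronger readings are tempting and not supported:
- The 8.6% figure for plain regression is not the error of this plan, which uses multilevel models when the check is positive.
- The article does not say that the model is chosen separately for each outcome. It describes one assessment.
- A family-level error of 6.2-8.6% would need both parents of every family in one pooled model. Fathers are optional, lone parenthood is a qualifying criterion in both countries, and pooling is not stated. A mothers-only model has little family clustering.

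It might also be said that an analysis plan will settle this. But the article states the rule itself, and a plan that followed it would carry the problem forward.

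**Conclusion.** The point holds, at modest size. The rule lets the randomised unit be dropped on a check that has no stated criterion and that, if it were a 5% test, would have low power. Nothing else in the article protects the regression branch.

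For assumed ICCs of 0.05-0.10, the two-step type I error is about 5.3-6.5% against a nominal 5%. It is about 5.5% or less with 60 HPs per arm in each trial, and there is no inflation if the ICC is near zero. Individual trials that end in plain regression carry more, up to about 8.7% in the least favourable setting in the table. The family level adds to this only when several members are modelled together.

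A reader might infer that the primary inference is seriously invalid. The figures do not support that. This should be fixed because the rule is wrong in principle and cheap to replace, not because the expected error is large.

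**What to change.** Delete the two-step rule. State, before unblinding, that every between-arm analysis allows for HP, and for family whenever more than one member is in the model, whatever ICC is estimated. Either of two methods will do:
- a mixed model with random effects for these levels and a small-sample degrees-of-freedom correction; or
- cluster-robust standard errors at HP level, with a small-sample correction. Because families are nested within HPs, this also covers the family level.

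Report the ICC descriptively, without using it to choose the model. With one to three families per HP, a variance estimate of zero is likely at times, so say in advance that it does not trigger a return to plain regression.

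The cost is a sentence or two and no new data. Intervals may be slightly wider: with three families per HP and ICC 0.05, the standard error rises by √1.10 = 1.05, about 5%, which is what the design requires if that correlation exists.

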### Participants

For a family to participate, at least the mother has to agree to participate in the study. If the father of a family is also present and agrees to participate, he can be registered separately by the HP. Families will be enrolled by the HP once the mother agrees to participate in the study.

*In Austria,* eligible families should a) meet one of the criteria of low SES (defined as: no partner or receipt of financial benefits or low education), b) expect a child (gestational age between the 18^th^ and 22^th^ week) and c) own a smartphone. *In Germany,* eligible families are those who a) meet at least one of the psychosocial burden factors (see Table 1), b) have a child at the age between 0-12 months, c) own a smartphone, and d) receive home-visiting support from a HP for a period of at least 12 weeks.

**Table 1 Tab1:** List of psychosocial burden factors as part for the inclusion criteria in Germany

**Psychosocial burden factors**	• financial problems • single parenthood • mental illness of one parent • underaged mother • insecure living situation • traumatic life events in the past • social isolation / lack of integration • birth of multiples and rapid succession of births • premature birth of the child • regulatory disorder of the child • chronical illness, developmental delay and/or disability of the child • relationship distress

In both countries, families will be excluded from the study if they meet at least one of the following exclusion criteria: a) mother is younger than 16 years; b) acute mental health problems that hamper the ability to participate (e.g., suicidality, mania); c) chronic disease that can influence behavior related to energy balance (diabetes, pre-eclampsia, etc.) or require a complex diet, d) insufficient knowledge of the German language (which does not allow the use of the app and the completion of the questionnaires) or e) other reasons that do not allow the correct use of the app, counseling or completion of the questionnaires. Each family will receive €50 for participation if all questionnaires are completed.

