In *Germany*, HPs will be able to register online and complete an online questionnaire containing the consent to the study, the screening for inclusion and exclusion criteria, as well as questions about their professional background. Eligible HPs will be randomized to one of the two study conditions, contacted via email with the information about their group assignment, and sent forms and materials by mail. Afterwards, the study coordination will get in contact with the HPs via telephone and conduct a 20-30 minutes briefing with instructions on the study materials (onboarding). If they have been assigned to the intervention condition, they will receive a five-hour online training for the blended counseling. In a second step, the HPs will screen each of their families for the eligibility criteria, inform potential families about the study, and provide information material, as well as data protection policies to interested families. HPs will be able to register families online. The participating families receive an individualized link for the baseline assessment (t0) via mail. After the families have completed the assessment, the HP and the participants receive a message to start the intervention and – in case of the intervention condition – a download guide for the app. After 12 weeks, the families receive the link for the post assessment (t1) via email. Three months after the end of the intervention, participants will be asked to complete a follow-up online questionnaire (t2). In case of non-response, participants will be reminded via email and telephone as well as through the HP. In both countries, the app access will be deactivated after the intervention period for the intervention group and (again) activated for each participant (also for the control group) after the last assessment (t2) is completed.

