### Outcomes

Our primary outcome will be body composition measured through body mass index (BMI) of the family members (self-reported, the mother’s, if available father’s and the child’s height and weight). Secondary outcomes will be eating behavior (i.e., eating styles), physical activity, and psychological factors (i.e., depression, emotion regulation, parental stress) that are associated with the family’s well-being and influence eating behavior and physical activity. Information about the children (height, weight, breastfeeding) is collected through the mothers. Since the project primarily intends to reach psychosocially burdened families another focus lies on socio-demographic characteristics and socio-economic stressors (e.g., whether families receive social support, health status, crowded living conditions, and the migrant status of the parents). Data will be gathered at three (Germany) or four (Austria) time points. Tables 2 and 3 provide an overview of the included measurements.

**Table 2 Tab2:** Data collection at different time points during the study in Austria

Questionnaire	t_0_	t_0.5_	t_1_	t_2_
	18^th^ to 22^nd^ week of pregnancy	35^th^ -37^th^ week of pregnancy	8 weeks pp	3 months after t_1_
Socio-demographics	x			
Weight of the parent	x	x	x	x
Child’s weight and height			x	x
DEBQ	x	x	x	x
FFQ	x	x	x	x
IPAQ	x	x	x	x
EPDS	x	x	x	x
DERS-SF	x	x	x	x
ECR-RD		x		
GSE	x	x	x	x
CTS		x		
PSI-SF			x	x
PBQ			x	
I-FEEL				x
Regulatory Disorders				x
MAUQ			x	

*DEBQ* Dutch Eating Behaviour Questionnaire, *FFQ* Food Frequency Questionnaire, *IPAQ* International Physical Activity Questionnaire, *EPDS* Edinburgh-Postnatal-Depression-Scale, *DERS-SF* Difficulties in Emotion Regulation Scale, *ECR-RD* Experiences in Close Relationships, *GSE* General Self-Efficacy Scale, *CTS* Childhood Trauma Screener, *PSI-SF* Parenting Stress Index, *PBQ* Postpartum Bonding Questionnaire, *MAUQ* mHealth app usability questionnaire, *pp* postpartum

**Table 3 Tab3:** Data collection at different time points during the study in Germany

Questionnaire	t_0_	t_1_	t_2_
	0-12 months pp	3-15 months pp	3 months after t1
Socio-demographics	x		
Weight of the parent	x	x	x
Child’s weight and height	x	x	x
DEBQ	x	x	x
FFQ	x	x	x
IPAQ	x	x	x
EPDS	x	x	x
DERS-SF	x	x	x
ECR-RD		x	
GSE	x	x	x
CTS	x		
PSI-SF	x	x	x
PBQ	x	x	x
I-FEEL			x
Regulatory Disorders			x
MAUQ		x	

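### German trial: the one adjustment named, baseline outcome, does not account for a 0-12 month spread in time since birth at entry, which arm-aware recruitment could make unequal between arms

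*Protocol article*

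**What the plan says.** All references are to the protocol article.

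- **Participants:** German families qualify if they "have a child at the age between 0-12 months" (among other criteria).
- **Procedure:** "After 12 weeks, the families receive the link for the post assessment (t1) via email". Table 3 in Outcomes accordingly places t0 at 0-12 and t1 at 3-15 months postpartum.
- **Randomization:** the unit is the healthcare professional (HP), and the sequence is "pre-stratified for the two trials". On timing: "Participating HPs will be randomly assigned to one of the two study arms and will be informed about the assignment immediately".
- **Procedure:** in Germany, HPs screen and register families after they have been randomised and, in the intervention arm, trained.
- **Blinding:** "Families will be told about the group assignment of the HPs during the recruitment process".
- **Statistical analyses:** "analyses on intervention effects will be adjusted for baseline values of the outcome". No other covariate is named, and time since birth is not among the listed moderators.
- **Sample size calculation:** "Since both trials will initially be analyzed separately", so a country term would not stand in for entry time. The same section powers the infant outcome on a BMI z-score, whereas Outcomes names only BMI for the child.

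**The concern.** Two mothers with the same baseline weight, one two weeks after birth and the other at eleven months, would not be expected to change equally over the next 12 weeks. The Background itself says that many women shed the extra pregnancy weight by 12 months, so the protocol treats the entry window as a time of changing weight. Baseline weight mostly reflects differences between women and says little about time since birth. For infants, raw BMI is hard to compare across ages 0-12 months without reference to age.

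Two things follow. Variation in entry time that the model does not explain stays in the residual and costs some precision. More important, HPs choose which families to approach, and when, with their arm known. Intervention HPs also have a five-hour training step that control HPs do not. If child age at t0 came to differ between arms for such reasons, part of the natural weight course would be read as an intervention effect, or would mask one. Randomising HPs does not protect against this, because families enter afterwards.

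**Working it through.** **1. The plan's own figures.** Inputs from Sample size calculation: two-sided alpha 5%, power 80%, 100 families per arm, 20% dropout (80 analysable per arm), no design effect, targets of 2 kg and of 0.45 z-score (SD 1.0).

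- z-score: n = 2(1.960 + 0.842)² / 0.45² = 77.5, so 78 per arm; 78 / 0.8 = 97.5, so 98 (99 with the t-test). This agrees with 100.
- 2 kg: no SD is stated. Solving backwards, SD = 2 / (2.802 × √(2/80)) ≈ 4.51 kg (4.49 with the t-test). About 4.5 kg is used below as the implied value.

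**2. Assumed postpartum course.** The documents give none, so this is a declared assumption shown as a range. A mother carries A kg of excess at birth, which declines exponentially with time constant τ months. The expected change over 12 weeks (2.76 months) from entry at t months is

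change(t) = −A [exp(−t/τ) − exp(−(t + 2.76)/τ)],

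with A = 4, 6, 8 kg; τ = 1.5, 2.5, 4 months; t uniform on 0-12.

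**3. Spread, and precision lost.** R² = (SD of expected change)² / 4.49². Power is for 80 per arm and 2 kg, with residual SD 4.49 × √(1 − R²).

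| A (kg), τ (months) | Change, entry at birth | Change, entry at 12 months | SD over entry times | R² | Power after adjustment |
|---|---|---|---|---|---|
| 4, 4 (least) | −2.0 kg | −0.1 kg | 0.51 kg | 0.013 | 80.5% |
| 6, 2.5 (middle) | −4.0 kg | about 0 | 0.99 kg | 0.049 | 81.9% |
| 8, 1.5 (most) | −6.7 kg | about 0 | 1.46 kg | 0.105 | 84.1% |

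A wider set of curves (3-9 kg to lose, half-life 1.5-6 months) gives R² 0.002-0.12 and power 80.3-85.0%. The precision gain is therefore about 0 to 5 percentage points.

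**4. A systematic difference in entry.** As an illustration, one arm enrols uniformly over 2-12 months and the other over 0-12. Mean child age then differs by 7 − 6 = 1 month.

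| A (kg), τ (months) | Mean change, 0-12 | Mean change, 2-12 | Difference | Share of 2 kg |
|---|---|---|---|---|
| 4, 4 | −0.63 kg | −0.44 kg | −0.19 kg | 9% |
| 6, 2.5 | −0.83 kg | −0.44 kg | −0.39 kg | 19% |
| 8, 1.5 | −0.84 kg | −0.27 kg | −0.58 kg | 29% |

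The later-entering arm appears to lose less weight. If that is the intervention arm, the effect is understated; if it is the control arm, it is overstated.

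**5. Chance imbalance, for comparison.** With uniform entry, the SD of child age is 12/√12 = 3.46 months. The 95% range for the difference in arm means is 1.96 × 3.46 × √(2/80) ≈ 1.1 months, ignoring clustering. The standard error already allows for differences of that kind.

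**The case against.** The strongest reply is that a journal article need not carry a full covariate list. The sentence in Statistical analyses does not exclude further covariates, and an analysis plan that is not shown may add them. That stands to this extent: a reader might infer that the model adjusts for baseline and nothing else, and the text does not say so. What can be said is that the article states an adjustment rule and the rule as stated does not cover entry time.

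The other side is also right on four further readings.

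- *Entry time dominates the outcome.* The documents give no figure for this, and the assumed curves attribute roughly 1-11% of the variance to it.
- *Randomisation should have been stratified on child age.* HPs are randomised before their families are recruited, so a family-level value does not exist at that point.
- *Any imbalance in child age is bias.* Chance imbalance is not. Only a difference produced by recruitment with the arm known would be.
- *The Austrian trial needs a matching gestational-age covariate.* Entry there is confined to weeks 18-22, and nothing in the documents makes a case for it.

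It is also fair that the 2-12 versus 0-12 month scenario is illustrative. Eligibility is the same in both arms, HPs are told to screen each of their families, and nothing shows that such a gap will occur. Nor does one covariate cure all selection that may follow unblinded recruitment. What remains is that this particular route is open, foreseeable and cheap to close.

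**Conclusion.** The point holds for the German trial as a limited but worthwhile improvement. The wide entry window, the 12-week interval, the single named adjustment and recruitment with the arm known all stand in the article. Together they leave the primary contrast exposed to a systematic difference in time since birth that baseline adjustment would not remove.

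The main reason to act is protection against that difference: about 0.2-0.6 kg, or roughly 10-30% of the 2 kg target, in the illustrative case. Precision is a secondary and modest reason (power from 80% to about 80.5-84%). These sizes rest on the assumed weight curves, uniform entry and a back-solved SD of about 4.5 kg; the direction of the argument does not. The calculations ignore clustering by HP, as the plan's sample size does.

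**What to change.** For the German trial:

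1. Prespecify child age (time since birth) at t0 as a covariate in the maternal and child primary-outcome models, alongside the baseline outcome and in a flexible form, for example a spline with three knots.
2. Report the distribution of child age at t0 by arm.
3. State in Outcomes that child BMI is analysed as the age-standardised z-score already used in Sample size calculation.

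The cost is a few degrees of freedom and some wording. Exact child age at t0 must be recorded; the article shows only that the 0-12 month band is checked for eligibility, so this should be confirmed. The change should be fixed before outcome data are seen by arm, since the same covariate added later would look data-driven.
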